## Method

### Study design

A single-blinded, 6-month follow-up, parallel-group cluster randomized controlled trial with 1:1 allocation ratio will be implemented in Changsha, China. This study will be conducted, analyzed and reported according to the Consolidated Standards of Reporting Trials (CONSORT) 2010 statement: extension to cluster randomized trials [19] and strict adherence to the Standard Protocol Items: Recommendations for Interventional Trials (SPIRIT) guidelines (Details of the SPIRIT 2013 Checklist is provided in Additional file 1) [20]. Ethical approval for the study was obtained from the Ethics Committee of Xiangya School of Public Health, Central South University (No. XYGW-2017-02). All participants will be adults who provide informed consent online prior to receiving the interventions in both groups and all data will be analyzed anonymously.

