### Interventions for control and intervention groups

We will provide the participants in both experimental groups with an app-based parenting education program that targets training on pediatric diseases and parenting skills but excludes information about unintentional injury prevention. The education program will use short essays, games, cartoons and videos to disseminate knowledge and skills about optimal parenting of young children. The content, interaction, survey and feedback, and personal module of app will be identical for both groups.

The intervention group’s app will have additional components that are focused on unintentional injury prevention. As detailed below, the intervention group’s app will have features geared particularly toward parenting and education on child injury prevention, including some features that rotate seasonally (e.g., drowning prevention in summer).

Both parenting and injury prevention features in the app will be available throughout the intervention time period so that the users can retrieve any information they want on a repeated basis.

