### Primary outcome measure

The primary outcome measure will be the incidence of unintentional injury among preschoolers in the prior 3 months, as collected both at 3-month and 6-month follow-up visits. Following previous epidemiological studies [32], we define an injury event as one that meets any of the following criteria: (i) child receives medical treatment by a doctor or other medical professional following an injury; (ii) child receives first aid by a family member, teacher or other non-medical staff following an injury (e.g. takes medication, receives massage or hot compress); and/or (iii) child is restricted from school or other activities, or is kept in bed/rest for more than a half-day following an injury.

Our primary outcome variable will be unintentional injury incidence, calculated as$$ \frac{\mathrm{Number}\ \mathrm{of}\ \mathrm{preschoolers}\ \mathrm{experiencing}\ \mathrm{an}\ \mathrm{unintentional}\ \mathrm{in}\mathrm{jury}\ \mathrm{in}\ \mathrm{the}\ \mathrm{prior}\ \mathrm{three}\ \mathrm{months}}{\mathrm{Total}\ \mathrm{number}\ \mathrm{of}\ \mathrm{children}\ \mathrm{that}\ \mathrm{the}\ \mathrm{recruited}\ \mathrm{caregivers}\ \mathrm{look}\ \mathrm{after}}\kern0.5em \times \kern0.5em 100\% $$

Given cultural patterns in China, we anticipate most participants will be caregivers who oversee one single child who meets inclusion criteria, and most families will have just one preschooler when the caregivers are recruited. If an adult caregiver takes care of more than one preschooler, we will enroll only the youngest child when calculating injury incidence. Along with recording injury counts (frequency), we will code external causes of unintentional injury based on the International statistical Classification of Diseases and related health problems 10th revision (ICD-10) [33].

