### Data collection

Data will be collected at three time points: baseline, 3 months post-intervention, and 6 months post-intervention. All data will be collected through app-based online surveys and will be stored in the backend database of app with password limiting the access. If caregivers fail to complete app-based surveys, we will provide printed paper questionnaires to participants through the support of facilitating teachers. In addition, an independent app-based survey among a sample of 100 caregivers will be conducted at each time period to test the reproducibility of collected data.

We also will collect compliance data through electronic strategies embedded in the app. These will include frequency of login, length of time using the app at each log-in, the number of knowledge disseminations used and listed as bookmarks, the number of published comments, and so on.

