### Data analysis plan

Analysis will follow the intention-to-treat approach [38]. Descriptive data (mean, standard deviation, median, inter-quartile range, proportion) will be calculated to describe the characteristics of primary and secondary outcome measures and covariates. Chi-square test (categorical outcomes) and two sample independent *t*-test (continuous outcomes) will examine differences in unintentional injury incidence and other outcome indicators between the two arms at each time point (baseline, 3 months, 6 months). Chi-square test (categorical outcomes) and analysis of variance for repeated measurement data (continuous outcomes) will detect differences across the three time points for each arm.

The primary analysis will be conducted through Generalized Estimation Equation (GEE) models, which will test the effectiveness of the app-based intervention based on the interaction of group (intervention vs. control) with time (baseline, 3 months, 6 months) after adjusting for socio-demographic variables (age, sex, household income) and compliance to the intervention (use of the app-based interventions).

Missing values will be imputed using the Expectation Maximization algorithm (EM). To test the robustness of results, sensitivity analysis will be conducted by comparing primary and secondary outcome data collected through the online app-based survey and those completed using a printed questionnaire survey. Statistical analysis will be performed through Stata/IC 12.1. Statistical significance will be based on 2-sided tests at the level of 0.05.

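### The within-arm tests across the three surveys use a chi-square for categorical outcomes, which ignores that the same children are measured three times (minor, secondary analysis)

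*Protocol article*

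**What the plan says.** The Data analysis plan of the protocol article sets three layers of testing: comparisons between arms at each time point, comparisons over time within each arm, and a primary GEE model. The within-arm layer reads: "Chi-square test (categorical outcomes) and analysis of variance for repeated measurement data (continuous outcomes) will detect differences across the three time points for each arm".

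These surveys are repeated on one cohort. The Data collection section states: "Data will be collected at three time points: baseline, 3 months post-intervention, and 6 months post-intervention". Under Participant recruitment, the consenting caregiver completes the baseline survey, which already asks about injury in the past 3 months. Under Primary outcome measure, each caregiver contributes one child, and the outcome is "the incidence of unintentional injury among preschoolers in the prior 3 months, as collected both at 3-month and 6-month follow-up visits". It is a proportion of children with at least one injury, so it is binary for each child.

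Effectiveness is assigned to a different analysis. The GEE tests it "based on the interaction of group (intervention vs. control) with time (baseline, 3 months, 6 months"). The general significance rule is: "Statistical significance will be based on 2-sided tests at the level of 0.05".

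**The concern.** A Pearson chi-square on a table of three surveys by injured or not injured assumes that the three rows come from different children. Here they come from the same children. The plan recognises this for continuous outcomes, where it names a repeated-measures analysis of variance, but not for categorical ones, which include the primary outcome and the attitude items. The chi-square is the test already named for independent groups one sentence earlier, and no variant for matched data is mentioned.

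What is at stake is the calibration of the within-arm p-values. Ignoring positive correlation overstates the variance of a change over time, so the p-values are too large on average and real changes are missed more often than they need be. The decision about the app does not rest on these tests.

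**Working it through.** **Inputs.**
- Nominal level 0.05, two-sided (Data analysis plan).
- Three surveys of the same children, so 2 degrees of freedom (Data collection).
- Incidence p = 23% and n = 1181 per arm (Sample size).
- Within-child correlation ρ between any two surveys: **assumed**, because the protocol gives none. The range shown is 0 to 0.5.

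The protocol gives no figure for the within-arm test, so there is none to reproduce. The 1181 is taken as stated. It does not reproduce exactly from the stated inputs (763 per arm before clustering × [1 + 139 × 0.005] = 763 × 1.695, about 1294), but nothing here turns on that, and the large-sample null size below does not depend on n.

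**Step 1: variance of a change.** For two surveys s and t of the same n children at equal incidence p:

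Var(p̂_s − p̂_t) = 2p(1−p)(1−ρ)/n

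The chi-square works with 2p(1−p)/n, which is correct only at ρ = 0. With equal correlation between surveys and no change over time, the statistic therefore behaves like (1−ρ) times a chi-square with 2 df.

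**Step 2: true size.** The 5% critical value on 2 df is 5.991, and the upper tail on 2 df is exp(−x/2). Hence

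size = exp(−5.991 / [2(1−ρ)])

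| ρ (assumed) | Exponent | True size | Simulation (n = 1181, p = 0.23, 100,000 runs) |
|---|---|---|---|
| 0 | −5.991/2.0 | 5.0% | 4.9% |
| 0.1 | −5.991/1.8 | 3.6% | 3.5% |
| 0.2 | −5.991/1.6 | 2.4% | 2.4% |
| 0.3 | −5.991/1.4 | 1.4% | 1.4% |
| 0.5 | −5.991/1.0 | 0.25% | 0.27% |

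**Step 3: power lost, for one assumed path.** Let incidence run 23%, 21%, 19%. The mean is 0.21 and the sum of squared deviations is 0.02² + 0 + 0.02² = 0.0008. At ρ = 0.3 the noncentrality is

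λ = 1181 × 0.0008 / (0.21 × 0.79 × 0.7) = 0.9448 / 0.1161 = 8.14

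Cochran's Q rejects above 5.991, which gives 73% power. The chi-square in effect rejects only above 5.991/0.7 = 8.56, which gives 54%. At ρ = 0.2 the figures are 66% and 55%. At ρ = 0 both are 56%.

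**The case against.** The strongest reply is that little depends on these tests. The plan gives them only the task of detecting differences across time points. It judges effectiveness from the group-by-time GEE, and the Abstract says the same. In that contrast a season effect shared by both arms cancels on the model's scale, and GEE can allow for repeated measures. All of this stands, and it sets the weight of the point. It does not make a test for independent samples right for paired data.

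It can also be said that the article does not name the chi-square variant. That is weak: the same term serves the independent-group comparison in the preceding sentence, and repeated measurement is mentioned only for continuous outcomes.

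A reader might infer something stronger: that season makes the within-arm tests produce false claims of benefit. With 1181 children, no app effect and zero within-child correlation, an assumed path of 23%, 23%, 18% gives significance about 88% of the time, and 23%, 23%, 20% about 43%. The documents do not support that reading, for four reasons.
- These rates are power to detect a change over time that is real. They become errors only if the change is credited to the app, and no section does that.
- In the 43% case exactly one arm is significant in 2 × 0.43 × 0.57 = 49% of trials, but only half of these (0.43 × 0.57, about 25%) favour the app.
- The article says of the intervention app only that it has added features, "including some features that rotate seasonally (e.g., drowning prevention in summer"). It does not say that overall injury incidence is seasonal, and it gives no calendar dates.
- The rotating content is part of the intervention, and the same section says the app's features remain available throughout.

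**Conclusion.** The point holds as a minor correction to a secondary analysis. For categorical outcomes, including the primary one, the named within-arm test assumes an independence that the design does not have, and the same sentence avoids this mistake for continuous outcomes. At a nominal 5% the true size is about 3.6%, 2.4% and 1.4% for within-child correlations of 0.1, 0.2 and 0.3.

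A reader might take a miscalibrated test to mean too many false positives. Within-child correlation works the other way: the test is conservative and loses power.

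The sizes rest on assumptions: the correlations themselves, equal correlation between surveys, complete data, and children otherwise independent within an arm. A preschool effect that is constant over the three surveys largely cancels from a comparison over time. One that shifts between surveys would not cancel and would push the size upwards, and the protocol gives no basis for sizing it.

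Season and ageing do limit what a within-arm change can mean, which justifies a sentence on interpretation. They do not show that the plan misattributes such a change. The sample size and the primary GEE contrast are not affected by this error.

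**What to change.** In the Data analysis plan, change the sentence on differences across the three time points in one of two ways:
1. For categorical outcomes, name a method for repeated measurements. This can be the time term of a GEE fitted within the arm, or Cochran's Q for binary items. Cochran's Q does not apply directly to the four-option attitude items, which need a GEE for categorical responses or a stated dichotomy.
2. Drop the within-arm test for these outcomes and report each arm's incidence or proportion at baseline, 3 and 6 months with confidence intervals.

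With either choice, add one sentence: change within an arm also reflects season and the children's ageing and is not evidence of an app effect; effectiveness is judged from the between-arm group-by-time GEE already planned.

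The cost is analysis wording only. No data, sample size or objective changes.

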### School recruitment

This study plans to recruit participants from 20 preschools in Changsha, China, 10 public and 10 private (note: preschools enroll children ages 3–6 years in China) (Figs. 1 and 2). All schools in Changsha with more than 100 enrolled students will be regarded as eligible schools and will receive an official invitation letter along with related materials about this project. Each facility that agrees to participate will select one teacher to coordinate recruitment of study participants. To avoid unwanted contamination within the same preschool, we will randomly allocate to the intervention versus control group at the school level, stratifying by public/private, such that 10 preschools will be in the intervention group and 10 in the control group, with each group including 5 public preschools and 5 private preschools.

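### The primary GEE's stated covariates omit the public/private randomisation stratum, and nothing in its description makes preschool the clustering unit

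*Protocol article*

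**What the plan says.** School recruitment in the protocol article gives the design: "This study plans to recruit participants from 20 preschools in Changsha, China", randomised by school and "stratifying by public/private, such that 10 preschools will be in the intervention group and 10 in the control group", which means five public and five private preschools per arm. Study design calls it a "parallel-group cluster randomized controlled trial with 1:1 allocation ratio". Sample size uses an ICC of 0.005 for a preschool of 140.

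Data analysis plan fixes the primary test: "The primary analysis will be conducted through Generalized Estimation Equation (GEE) models". The test is "based on the interaction of group (intervention vs. control) with time (baseline, 3 months, 6 months"), and the model is fitted "after adjusting for socio-demographic variables (age, sex, household income) and compliance to the intervention (use of the app-based interventions"). The last general statement is "Statistical significance will be based on 2-sided tests at the level of 0.05".

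Public/private is not among the covariates. The section does not name preschool as a level or cluster, and it is silent on working correlation, variance estimator, reference distribution and degrees of freedom.

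**The concern.** Two parts of the design do not reach the written primary analysis.

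- **Preschool clustering.** The GEE is described only through group and time. A reader could implement it with the child as the cluster and the three reports as repeated measures. That handles correlation within a child but treats children in one preschool as independent, although the preschool was randomised.
- **The stratum.** The adjustment set is an explicit list, and it leaves out the one variable that restricted the randomisation. Variation between public and private preschools then stays in the error term of any contrast it affects.

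At stake is mainly the false-positive rate of the primary test. The precision of contrasts at 3 or 6 months is a smaller issue.

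**Working it through.** **Inputs from the protocol article.** 20 preschools, 10 per arm, five public and five private in each; ICC 0.005; control incidence 23%; effect size 0.75, read here as a risk ratio (0.23 × 0.75 = 0.1725); 1181 per arm before attrition; two-sided 0.05.

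**Assumptions.** 118 analysed children per preschool (1181/10); the share of preschool variance that changes over time; the public/private gap. The documents give no figure for the last two, so ranges are shown.

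**The plan's own figures.** There is no stated error rate to reproduce. The plan's design effect is 1 + (140 − 1) × 0.005 = 1.695, or 1 + (118 − 1) × 0.005 = 1.585 at 118 children. With 763 per arm before clustering, 763 × 1.695 = 1293, not 1181. That mismatch is a separate matter.

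**Step 1: clustering on the child only.** Null trials were simulated with three reports per child, using the 2-df group-by-time chi-square test at ICC 0.005.

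| Share of preschool variance that changes over time | Type I error |
|---|---|
| 0 (constant) | 5.5% |
| 0.5 | 9.7% |
| 1 (fully time-varying) | 14.3% |

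A constant preschool effect cancels from a change contrast; a time-varying one does not.

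**Step 2: clustering on preschool, sandwich variance.**

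- Group by time, stratum omitted, gap constant over time (half the preschool variance time-varying): uncorrected chi-square 10.0-11.6%. The corrected test multiplies the Wald statistic by 0.9 × 17/36 and refers it to F on 2 and 17 df; its error is 4.2-5.7%.
- Single-time group effect, uncorrected z: 8.8-9.7% with the stratum in the model, and 8.5% with it omitted and no gap. With the stratum and a small-sample t: 4.7-5.5%.

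**Step 3: the stratum in a single-time contrast.** The variance of a preschool proportion is 0.23 × 0.77 × (0.005 + 0.995/118) = 0.1771 × 0.01343 = 0.00238. A public/private gap of d adds (d/2)².

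- d = 4 points: √[(0.00238 + 0.0004)/0.00238] = 1.08
- d = 6 points: √[(0.00238 + 0.0009)/0.00238] = 1.17

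The standard error is therefore 8-17% wider without the stratum. In simulation with the uncorrected z-test and the stratum omitted, error moves from 8.5% (no gap) to 6.4%, 3.4% and 0.3% at log-odds gaps of 0.2, 0.4 and 0.8.

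**Step 4: the stratum in the group-by-time test.** A time-constant gap cancels (Step 2). Starting from a log-odds gap of 0.4, growth of 0.4 over follow-up gives 8.3% uncorrected and 3.6% corrected; growth of 0.8 gives 5.5% and 2.5%.

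**Step 5: cost of a t reference.** For the planned single comparison, SE = √[(0.1771 + 0.1427) × 1.585/1181] = 0.0207, and 0.0575/0.0207 = 2.78. Power is Φ(2.78 − 1.96) ≈ 79% with z, and about Φ(2.78 − 2.10) ≈ 75% with t on 18 df.

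**The case against.** **The article may simply be condensed.** It names no variance estimator, so it neither adopts nor excludes a small-sample correction, and such detail is commonly left to an analysis plan that is not shown. This stands. A reader might infer that the trial relies on uncorrected GEE inference, but the documents do not say so. The 8-12% describes one possible implementation.

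**Clustering is not ignored by the trial.** Study design commits the analysis to the CONSORT extension for cluster trials, and Sample size uses a preschool ICC. This stands as evidence of intent. It does not settle what the GEE clusters on, because the section that defines the primary test describes it only through group and time.

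**The stratum figure belongs to another contrast.** The 8-17% is for a comparison at one time point, while the planned test is group by time. This stands. The assumed gap also strains the stated ICC. Between-preschool variance at 0.005 is 0.1771 × 0.005 = 0.00089, and a 6-point gap alone contributes 0.0009. Adding 4-6 points on top gives a total ICC of about 0.007-0.010.

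**Errors in both directions.** A reader might combine the points and conclude that the primary test is wrong both ways. That is not supported. An uncorrected sandwich narrows the standard error and an omitted stratum widens it. Both act on the same standard error and offset each other, and the widening largely drops out of the group-by-time test when the gap is constant. Omitting the stratum does not by itself create false positives.

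**Conclusion.** The point holds in a limited form. The stated covariate list omits the randomisation stratum, and as written nothing carries the preschool clustering into the primary test.

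- With child-only clustering, type I error lies between about 5% and 14% at ICC 0.005. At the lower end there is no inflation; the position in that range depends on how far preschool effects change over time, which the documents do not give.
- With preschool clustering and an uncorrected sandwich, error is roughly 8-12%, unless an omitted stratum gap pulls it down. A small-sample correction brings it close to 5%.
- The loss from omitting the stratum is an 8-17% wider standard error for single-time contrasts under an assumed 4-6 point gap. No loss is shown for the group-by-time test unless the gap changes over time.

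This is worth correcting before unmasking. It does not show that the trial will use an invalid analysis.

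**What to change.** Amend the wording of Data analysis plan:

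1. Add public/private to the primary model's covariates, with its interaction with time if a changing gap is plausible.
2. Name preschool as the GEE cluster, with the repeated reports of each child nested within it.
3. State a small-sample corrected variance (Kauermann-Carroll or Fay-Graubard) with a t or F reference on about 17-18 df: 20 preschools less two arms, less one more for the stratum. Alternatively, add a cluster-level analysis of the 20 preschools as a check.

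No data collection changes, because preschool and type are known for every participant. Intervals become slightly wider, and design power falls from about 79% to 75% with a t reference on 18 df. For single-time contrasts the stratum term recovers some precision if public and private preschools differ.

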### Sample size

Sample size was calculated based on our primary hypothesis, to detect a difference between the intervention and control groups in unintentional injury incidence among preschoolers in the prior 3 months. Previous studies reported an unintentional injury incidence of 25.5% among preschoolers in central China in the past 1 year [22] and an effect size of 0.64 between intervention and control groups [23]. Considering 1 year recall periods underestimate injury rates by 55 and 72% (most are minor injuries) compared with one-month recall periods [24, 25], and use of a strict operational definition that restricts injury events to those that cause activity restriction of 1 day or longer or are treated by a doctor or other medical professional substantially undercounts injury events (typically minor or moderate injuries) [26], we assume unintentional injury incidence among preschoolers in the past 3 months will be 23%. On the basis of a previous report [27], we estimate an intra-class correlation (ICC) of 0.005 within a preschool of 140 students. Predicting an incidence of 23% in the control group, an effect size of 0.75 between intervention and control groups, and an ICC of 0.005, α = 0.05, 1-ß = 0.80, a minimum sample size of 1181 caregivers is needed for each group. Conservatively estimating an attrition rate of 10% in the six-month follow-up study, we will require a recruited sample size of 1323 each group. In total, therefore, we will enroll 2626 participants. Since most preschools have far more than 100 students enrolled, 20 preschools are amply sufficient to recruit the needed sample size.

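### The stated 80% power was derived for a single between-arm comparison, not for the group-by-time interaction that is the declared primary test

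*Protocol article*

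**What the plan says.** Three sections of the Protocol article bear on this.

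- **Sample size.** The calculation is "to detect a difference between the intervention and control groups in unintentional injury incidence among preschoolers in the prior 3 months". Its inputs are a control incidence ("we assume unintentional injury incidence among preschoolers in the past 3 months will be 23" per cent), "an effect size of 0.75 between intervention and control groups, and an ICC of 0.005", and "α = 0.05, 1-ß = 0.80". The ICC is attached to a preschool of 140 pupils. The result is 1181 caregivers per group before attrition.
- **Primary outcome measure.** The outcome is 3-month incidence "as collected both at 3-month and 6-month follow-up visits". Neither visit is ranked above the other.
- **Data analysis plan.** The primary analysis is a GEE model whose test of effectiveness is "based on the interaction of group (intervention vs. control) with time (baseline, 3 months, 6 months"). On error control it says: "Statistical significance will be based on 2-sided tests at the level of 0.05".

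**The concern.** The sizing calculation and the primary test address different hypotheses. The first compares two proportions at one time. The second asks whether the change from baseline differs between arms. With time as three categories that means two parameters, 3 months against baseline and 6 months against baseline.

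Subtracting a binary baseline adds its sampling error and removes whatever is shared between visits. The balance depends on how strongly a child's reports, and a school's rates, correlate over time. A joint test also spends a second degree of freedom but draws on both follow-ups. None of this enters the sample size, so the reader cannot tell what power the declared test has.

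The second consequence concerns reporting. A joint test yields a p-value without one effect size or direction, and the article does not say which term would carry the conclusion.

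**Working it through.** **Inputs from the article.** Control incidence 23%; effect size 0.75, read as a risk ratio, so 0.75 × 23% = 17.25%; ICC 0.005; two-sided 0.05; 10 schools per arm; 1181 analysed per arm.

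**Inputs assumed, because the article gives none.** Within-child correlation ρ of 0.1 to 0.3; cluster autocorrelation (CAC, the correlation of a school's effect between visits) of 0.8 to 1.0; no arm difference at baseline; 1181 per arm at every visit; normal reference.

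**Step 1: the plan's own figure.** Two proportions, 23% against 17.25%, need 763 per arm without clustering. With 140 per school the design effect is 1 + 139 × 0.005 = 1.695, giving 1294 per arm rather than 1181. With 1181/10 = 118.1 per school it is D = 1 + 117.1 × 0.005 = 1.5855, giving 1210. The printed 1181 is therefore reproduced only approximately, and only with the smaller cluster size. That is a separate matter; I use 118.1 per school below.

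**Step 2: power of the comparison that was sized.** Binomial variances are 0.23 × 0.77 = 0.1771 and 0.1725 × 0.8275 = 0.1427, sum 0.3198.

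- Variance of the difference: 0.3198 × 1.5855/1181 = 0.000429, SE 0.0207.
- z = 0.0575/0.0207 = 2.775; power = Φ(2.775 − 1.960) = 0.79.

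**Step 3: the interaction.** Within an arm, the visit means have variance p(1 − p)D/n and between-visit covariance K√[p₁(1 − p₁)p₂(1 − p₂)]/n, where K = ρ + 117.1 × 0.005 × CAC.

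Example for 6 months minus baseline, with ρ = 0.1 and CAC = 0.8, so K = 0.1 + 0.4684 = 0.5684:

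- Intervention arm: 0.3198 × 1.5855 − 2 × 0.5684 × 0.1590 = 0.3264.
- Control arm: 2 × 0.1771 × (1.5855 − 0.5684) = 0.3603.
- Variance (0.3264 + 0.3603)/1181 = 0.000581, SE 0.0241, z = 2.385, power 0.66.

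The joint test uses the noncentral chi-square on 2 df, with noncentrality δ′(LΣL′)⁻¹δ. The rows of L are (−1, 1, 0) and (−1, 0, 1), and δ holds the two interaction effects.

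**Step 4: the alternative contrasts.** The averaged contrast takes the mean arm difference over 3 and 6 months. Adjustment subtracts b times the baseline difference. The lower figure of each pair takes b = ρ (the child's own report only). The higher takes the full arm-mean slope, which also uses school-level correlation (0.34 to 0.53 under a sustained effect).

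Sustained effect (17.25% at both follow-ups); the single unadjusted comparison is 0.79 throughout:

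| CAC | ρ | Joint 2 df | 6 mo − baseline | Averaged, unadjusted | Averaged, adjusted | 6 mo, adjusted |
|---|---|---|---|---|---|---|
| 0.8 | 0.1 | 0.685 | 0.664 | 0.920 | 0.943–0.962 | 0.818–0.844 |
| 0.8 | 0.2 | 0.732 | 0.709 | 0.908 | 0.955–0.967 | 0.846–0.864 |
| 0.8 | 0.3 | 0.783 | 0.758 | 0.896 | 0.966–0.973 | 0.876–0.887 |
| 1.0 | 0.1 | 0.741 | 0.717 | 0.906 | 0.936–0.968 | 0.825–0.868 |
| 1.0 | 0.2 | 0.792 | 0.766 | 0.894 | 0.953–0.975 | 0.859–0.891 |
| 1.0 | 0.3 | 0.846 | 0.819 | 0.882 | 0.969–0.982 | 0.894–0.917 |

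Gradual effect (risk ratio 0.875 at 3 months, 0.75 at 6 months); the two 6-month columns above are unchanged:

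| CAC | ρ | Joint 2 df | Averaged, unadjusted | Averaged, adjusted |
|---|---|---|---|---|
| 0.8 | 0.1 | 0.560 | 0.702 | 0.744–0.790 |
| 0.8 | 0.2 | 0.607 | 0.683 | 0.770–0.803 |
| 0.8 | 0.3 | 0.661 | 0.664 | 0.799–0.821 |
| 1.0 | 0.1 | 0.616 | 0.679 | 0.730–0.805 |
| 1.0 | 0.2 | 0.670 | 0.661 | 0.765–0.825 |
| 1.0 | 0.3 | 0.732 | 0.643 | 0.806–0.851 |

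**Step 5: sensitivity.** On the log-odds scale the joint test is somewhat higher, 0.75 to 0.89 (sustained) and 0.60 to 0.78 (gradual) over the same cells. Widening to ρ of 0 to 0.5 and CAC of 0.5 to 1 gives 0.64 to 0.97 and 0.50 to 0.90.

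**The case against.** Five arguments can be made for the plan.

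1. *The interaction is not shown to be weaker.* A reader might infer that the trial is underpowered. The documents do not support that. With a sustained effect the joint test matches or exceeds 0.79 once within-child correlation reaches about 0.2 to 0.3. The article gives no correlation that would settle on which side the trial falls. This objection stands in full.
2. *A joint test does give one answer.* It gives one p-value, so it would be wrong to say that the plan yields no single result. What is missing is a single effect estimate.
3. *Type I error.* Testing both terms separately at 0.05 would raise the overall error to about 9% (null correlation between the terms 0.3 to 0.6). The article does not say this will be done, and joint or separate testing is a detail that an analysis plan may settle. It is no fault of this document.
4. *The interaction is a valid test.* Randomised arms are equal in expectation at baseline, so each term targets the treatment effect at its visit on the model's scale. Preferring baseline as a covariate is a matter of efficiency, not correction of an error.
5. *Averaging is not always better.* Without baseline adjustment, and with half the effect at 3 months, the averaged contrast falls to 0.64 to 0.70. That is below the simple 6-month comparison and in some cells below the interaction.

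None of these removes the mismatch. The sizing hypothesis and the primary test are both stated outright, so an analysis plan would have to change one of them or redo the power; it could not merely fill a gap.

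**Conclusion.** The point holds as a mismatch: the 80% was derived for a test other than the declared primary one. The joint interaction has about 0.68 to 0.85 power with a sustained effect and 0.56 to 0.73 with a gradual one, against 0.79 for the single comparison. These figures rest on the assumed correlations, equal arms at baseline, the difference scale and a normal reference. The direction of the discrepancy is not known, and the claim should not be read as one of low power. No contrast or visit is designated to supply the effect estimate.

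The case for a change does not depend on that direction. In every cell tabulated, under both effect patterns, each baseline-adjusted 1-df contrast has more power than the joint interaction.

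**What to change.** Make the primary test one pre-specified 1-df group contrast on follow-up injury incidence, with the baseline 3-month injury report as a covariate. It can be the average over 3 and 6 months, or 6 months alone; the latter stays closest to the existing sample size. Report group-by-time as secondary and restate the power for the chosen contrast.

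Adjusted power for the averaged contrast is about 0.94 to 0.98 with a sustained effect and 0.73 to 0.85 with a gradual one. For 6 months alone it is 0.82 to 0.92 under either pattern. All are before a small-sample correction for 20 schools. For scale, a t reference with 17 df lowers the fully adjusted averaged figure from 0.96–0.98 to 0.94–0.97.

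The cost is revised wording and one recalculation. No new data are needed, because the baseline survey already asks about injury in the past 3 months. Change over time becomes a secondary result, and averaging loses power if the effect builds slowly. The choice between the two contrasts should therefore be made, with its reason, before outcome data are seen.
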